### Outcomes

We use different machine learning techniques to predict treatment response based on DP data. To evaluate treatment response, we implement two different criteria. First, we follow the definition of the PREACT research group to achieve comparability with other subprojects. It follows the concept of clinically significant change as introduced by Jacobson & Truax.^29^ The shift from a dysfunctional to a functional mental condition is operationalised by achieving a Brief Symptom Inventory-General Severity Index (BSI–GSI) score of less than 0.56 at T20/posttreatment assessment. Additionally, the change observed from baseline to T20/posttreatment must be reliable, as defined by the Reliable Change Index (RCI). The BSI–GSI is a self-report measure assessed cross-sectionally at T20 and TPost as part of PREACT.

Second, we will use aggregates of EMA assessments on positive and negative affect (PANAS-X; 21) collected during measurement bursts at T20 and TPost as additional indicators of treatment response as EMA-based measures were shown to capture different aspects of symptom load (28).

To account for the complexity of ID, PREACT further included disorder-specific measures as secondary outcomes: The Hamilton Anxiety Rating Scale (HAM-A; 29), the Montgomery–Åsberg Depression Rating Scale (MADRS; 30), the Yale-Brown Obsessive Compulsive Scale (Y-BOCS; 31, 32) and the Clinician-Administered PTSD Scale for DSM-5 (CAPS-5; 33, 34).

Finally, for exploratory analyses, outcomes will depend on the respective research question, that is, single-beep scores of EMA constructs or cross-sectional self-reports of ER capacities.

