Our research objectives encompass predictive and exploratory hypotheses. First, in-line with PREACT, we aim to find out if we can predict non-response (NR) at T20 (ie, after 20 therapy sessions) and TPost (ie, after therapy end or 365 days if therapy lasts longer) with sufficient predictive accuracy (i.e. >75%) using a combination of EMA and passive sensing features collected during the first, 14-day assessment phase (T0). We expect that EMA-based features can better capture ER-related dynamics and are thus of greatest importance, but passive features will provide significant incremental value. We further hypothesise that EMA and sensing features both have an incremental predictive value beyond more elaborate (neuro)physiological markers and thus represent an ecologically valid substitute for implementation. Second, we aim to find out if symptom changes during CBT can be modelled using EMA and passive sensing, and how they relate to cross-sectional self-report and physiological information. We hypothesise that data actively and passively generated by personal electronic devices such as smartphones and wearables can be linked to neuroimaging-based markers of ER assessed in other subprojects of the research group.

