As outlined above, we are interested in the incremental value of DP and EMA data to less burdensome, cross-sectional self-reports. As a first step, we will construct a baseline model that relies exclusively on the cross-sectional information collected at enrolment (T0).

Predictors will mirror the variables listed in the main protocol^1^—emographics, clinical routine variables (ie, primary diagnosis, comorbidity, medication and previous CBT) and standard intake questionnaires. Separate models will be trained for our two prespecified outcomes (T20, TPost). The baseline cross-sectional models will be compared against four progressively richer model sets: (a) EMA-only models, (b) passive-sensor-only models, (c) EMA+passive-sensor models and (d) all data sources combined (T0+EMA + passive). Paired differences in area under the curve (with 95% CIs, DeLong test) will quantify improvements in discrimination of (non)-response.

To assess feature importance and increase interpretability of our models, we will implement model-agnostic SHapley values (SHAP, SHapley Additive exPlanations).

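### Both response criteria and the EMA predictors are patient self-report while passive sensing is not, so the planned comparisons cannot tell a real EMA advantage from shared reporting style

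*Protocol article*

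**What the plan says.** **Outcomes.** The article states: "To evaluate treatment response, we implement two different criteria". The first is clinically significant change on the BSI-GSI: a "score of less than 0.56 at T20/posttreatment assessment", together with reliable change from baseline. It is described as follows: "The BSI–GSI is a self-report measure assessed cross-sectionally at T20 and TPost". The second uses aggregated EMA positive and negative affect from the T20 and TPost bursts. The section adds that "PREACT further included disorder-specific measures as secondary outcomes", naming HAM-A, MADRS, Y-BOCS and CAPS-5.

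**Introduction.** EMA is defined as repeated self-report on the smartphone, and passive sensing as data from smartphone or wearable sensors. The objectives expect that "EMA-based features can better capture ER-related dynamics and are thus of greatest importance", with passive features adding to them.

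**Predictive analyses.** A baseline model on T0 cross-sectional data, including intake questionnaires, is compared with EMA-only, passive-only, EMA plus passive, and all-source models. The measure is the paired AUC difference for (non-)response, and SHAP values describe feature importance. On the target, the section says: "Separate models will be trained for our two prespecified outcomes (T20, TPost"). It gives time points and names no instrument.

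No section links the secondary scales to this comparison. Shared reporting is not among the limitations in the strengths-and-limitations list or the Discussion.

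**The concern.** Suppose some patients consistently endorse more distress than others with the same underlying state. That tendency raises their EMA negative affect at T0 and their BSI-GSI at T20. The reliable-change condition compares patients with themselves and cancels part of it. The requirement to fall below a fixed cut-off does not. Sensor features carry no such component.

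The second criterion does not help. It shares the instrument as well as the reporter with the EMA predictors, so EMA affect would be predicting EMA affect.

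A better AUC for EMA-only than for passive-only models, or SHAP rankings led by EMA, could then arise in two ways: EMA carries more information about treatment response, or it shares a reporter with the outcome. The Introduction offers only the first explanation. The study seeks markers that clinics can readily implement, and EMA costs patients eight prompts a day for 14 days, so the reading of this contrast matters.

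**Working it through.** **Figures in the plan.** 585 × 0.80 = 468, as stated. 468 × 0.75 = 351, against 350 stated, which is rounding. The 585 rests on the main protocol, which is not shown. The concern depends on none of these except through precision (step 4).

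**1. Who supplies each variable**

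| Element | Source |
|---|---|
| EMA predictors | patient report |
| Passive predictors | sensors |
| BSI-GSI label | patient report |
| EMA affect criterion | patient report, same instrument as the predictors |
| Baseline model | includes intake questionnaires |
| HAM-A, MADRS, Y-BOCS, CAPS-5 | only CAPS-5 is named as clinician-administered |

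**2. Size of the effect when features track T0 distress.** All inputs are assumed; 400,000 simulated patients, standardised scale.
- True distress: T1 = 0.5·T0 + √0.75·e − 0.8.
- Self-report at each time: √(0.85 − v)·T + √v·S + √0.15·e, where S is a stable style and v its share of variance.
- Entry: baseline above a cut-off of −1.0.
- Response: follow-up below −1.0 and a fall greater than 1.96·√(2 × 0.15) = 1.07.
- EMA = a·T0 + √v·S + noise. Sensor = a·T0 + noise. Both have unit variance and the same correlation a with true distress.

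AUC for non-response, EMA / sensor:

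| a | v = 0 | v = 10% | v = 20% | v = 30% |
|---|---|---|---|---|
| 0 | 0.498 / 0.500 | 0.530 / 0.500 | 0.565 / 0.501 | 0.596 / 0.500 |
| 0.3 | 0.520 / 0.520 | 0.550 / 0.516 | 0.578 / 0.513 | 0.609 / 0.507 |
| 0.5 | 0.532 / 0.532 | 0.559 / 0.526 | 0.587 / 0.517 | 0.615 / 0.508 |

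The EMA lead runs from 0.030 (0.530 − 0.500) at v = 10% to 0.107 (0.615 − 0.508) at v = 30%. On a label without S the two sources differ by at most 0.003. With no true signal and v = 30%, EMA has AUC 0.60 with the reliable-change condition and 0.62 with the cut-off alone, so that condition reduces the artefact only slightly.

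**3. Size when features track T20 severity.** Assumed: correlation 0.35, BSI-GSI means 1.1 and 0.8, SD 0.6, reliable change 0.35, cut-off 0.56; about 76% are non-responders.
- If style replaces noise in EMA, the lead is about 0.02, 0.04 and 0.06 at v = 5%, 10% and 15%.
- If style also dilutes EMA's true signal, it is 0.016, 0.032 and 0.051.
- With T0 BSI-GSI in both models, the diluted lead at 10% falls from 0.032 to 0.016. Where features track T0 severity instead, it falls to 0.004.

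**4. Precision.** The hold-out is 0.20 × 468 = 93.6, about 94 patients, which leaves 468 − 94 = 374. The simulated standard error of an EMA-minus-sensor AUC difference is about 0.09 with 94 patients, so about 0.09 × √(94/374) = 0.045 with 374. The 95% half-widths are 1.96 × 0.09 = 0.18 and 1.96 × 0.045 = 0.09. Both exceed the leads in step 3. They assume an outcome for every patient.

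**The case against.** **The label is not fixed to BSI-GSI.** A reader might infer that the comparisons use that label alone. The text does not say so: Predictive analyses names only time points, and Outcomes states two criteria. BSI-GSI is the only one with a binary rule, so it is the likely target, but that is an inference. This does not rescue the comparison, because the other criterion is self-report as well.

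**EMA-only against passive-only is not named as a formal test.** The stated comparator is the baseline model, whose intake questionnaires should already carry reporting style, so the steps from baseline to EMA-only or to all sources are partly protected. This stands. The importance hypothesis, however, has to be read from the unprotected contrast or from SHAP.

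**Dynamic features are less exposed.** The plan includes individual SDs, RMSSD, autocorrelations and cross-lagged parameters. A constant additive style cancels from these, though differences in how patients use the scale may not. This stands. The plan does not say that the importance claim will rest on these features rather than on means.

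**A secondary-scale check is imperfect.** Clinician ratings draw partly on what patients say, the scales are disorder-specific and may be missing for some patients, and step 4 shows that rank order alone would often flip by chance. All of this stands and shapes the fix.

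**The main protocol may deal with this.** It is not shown and may set out how secondary outcomes are analysed. But this article itself states the hypothesis, its explanation, the outcomes and the comparison.

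**Conclusion.** The concern holds as a limit on interpretation. With self-report on both sides, neither the EMA-only versus passive-only contrast nor the SHAP rankings can support the claim that EMA matters most because it captures emotion-regulation dynamics. Under assumed style shares of 5% to 15% the spurious lead is about 0.02 to 0.06 AUC, and about 0.03 to 0.11 at 10% to 30%. The direction does not depend on the set-up; the size rests on the assumed share, for which the documents give no figure.

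Two stronger readings are not supported. One is that the ranking would reverse on an outcome free of reporting style. With EMA's correlation with true severity held equal, the gap on a style-free cut-off-plus-change label is about 0.000 to 0.003; a clear deficit for EMA on that label (−0.004 to −0.015) appears only if style is assumed to dilute it. The other is that predicting BSI-GSI non-response is invalid. It is valid for that target, whatever the source of the predictors.

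**What to change.** In Predictive analyses:

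1. Name the response label used in each model comparison.
2. Add T0 + EMA and T0 + passive models, both including T0 BSI-GSI, so that the two sources are compared after the same adjustment for intake self-report. In simulation this at least halves the artefact without removing it.
3. Prespecify a sensitivity analysis that repeats the comparison on those listed secondary scales that are clinician-rated, adjusted for their T0 value, in patients who have them. State who rates each scale.
4. Report paired AUC differences, or the equivalent for continuous scores, with 95% CIs, and do not rely on rank order.
5. Report EMA mean-level features separately from dynamic ones (SD, RMSSD, autocorrelation).
6. Describe an EMA lead seen only on self-report outcomes as prediction of self-reported response, and list shared reporting as a limitation.

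The cost is rerunning planned pipelines on outcomes PREACT already lists, plus a few sentences. No new data collection is needed and the main response definition is unchanged. The drawbacks are incomplete availability of the scales, wide intervals, and clinician ratings that still partly reflect patient report, so the check narrows the ambiguity without closing it.

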### Data preprocessing and feature engineering

In its raw format, passive sensing data are usually not interpretable. Thus, depending on the data source, data format and research question, different data preprocessing and aggregation steps will be necessary.

GPS data are collected as tuples containing coordinates (ie, Latitude and Longitude values). To clean and preprocess the data and build ML features, we follow guidelines by Müller *et al* (35). We adapt them to our event-based sampling format, where GPS was assessed when a location change was detected. From GPS data, we will calculate movement patterns in predefined timescales, that is, location entropy, distance travelled or time spent at home.Passive data derived from the Withings Scanwatch will be further preprocessed where possible and necessary, as Withings does not provide raw data for most data sources (see table 1). Here, we align our preprocessing steps with guidelines for preprocessing sensor data (36). From continuous PPG-based heart ate data, we are able to build features like average HR, min/max HR and HR-zones. From the resting-state ECG,we can create more fine-grained features like HRV. For sleep, we will calculate features describing sleep quality, that is, sleep duration, proportion of sleep phases and sleep efficiency (i.e. sleep duration/ time in bed) per night. Activity features describe the amount of, or time in active or inactive states, that is, total number of steps or time spent walking/running/cycling and the amount of calories burned.For EMA data, we will calculate the RMSSD (that is, for emotional inertia or ER variability), individual SD and mean values. Further feature engineering steps for EMA are described in the *Analysis* section.

Depending on the research question and granularity of data aggregation, a certain compliance rate has to be met to be included in the analysis (ie, at least 50% of completed EMA beeps). Missing data imputation will also depend on the type of data and applied analyses.

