## Abstract

**ABSTRACT:**

**Introduction:**

Cognitive behavioural therapy (CBT) serves as a first-line treatment for internalising disorders (ID), encompassing depressive, anxiety or obsessive-compulsive disorders. Nonetheless, a substantial proportion of patients do not experience sufficient symptom relief. Recent advances in wearable technology and smartphone integration enable new, ecologically valid approaches to capture dynamic processes in real time. By combining ecological momentary assessment (EMA) with passive sensing of behavioural and physiological information, this project seeks to track daily fluctuations in symptom-associated constructs like affect, emotion regulation (ER) and physical activity. Our central goal is to determine whether dynamic, multimodal markers derived from EMA and passive sensing can predict treatment non-response and illuminate key factors that drive or hinder therapeutic change.

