*Affect*: Participants were asked about their current affective state. The 17 items contain the PANAS-X (21) subscales, with additional single items on loneliness, fatigue and shyness. At each prompt, they were asked to rate on a scale from 1 to 7 how much they currently felt the respective affect.*Emotion Regulation*: At each beep, participants were asked to rate the intensity and controllability of their most negative thought since the last beep. Then we assessed the use of different ER strategies since the last beep using a German translation of the Regulation of Emotion Systems (RESS–EMA) scale,^24^ with six items covering reappraisal, rumination, suppression, distraction and relaxation. We implemented an additional item on acceptance.*Situational Context:* Self-constructed. To assess the situational context, we developed a custom measurement. Participants were asked to specify activities they had pursued in the preceding 2 hours from a given set of nine common activities. Participants were able to select multiple options simultaneously. The options were influenced by the DIAMONS scale and a comparable long-term digital phenotyping study.^25 26^ Here, we aimed to find a balance between sparsity of items and a high degree of situational coverage. Subsequently, they were asked to evaluate how much they enjoyed the respective activities.*Social Context:* Self-constructed. Participants were asked if they had social contacts since the last beep (online/ in person/ phone) and how agreeable the contact was.*Significant Events:* Self-constructed. Patients were asked to think about the most important event since the last beep and how pleasant they perceived it.*Physical fitness:* Self-constructed. Participants were asked how physically healthy they had felt today on the last beep of the day.*Therapeutic Agency*: We constructed four items based on the Therapeutic Agency Inventory (TAI)^27^ to assess Therapeutic Agency (TA) in everyday life. The original TAI contains three subscales, covering in-session activities, passivity towards the therapist and out-of-session activities. As we were interested in assessing TA in everyday life, our TAI–EMA items are based on the ‘out-of-session activities‘ subscales and cover cognitive and behavioural aspects of TA.*ECG Control:* During measurement bursts, patients were asked two times day to conduct a resting-state ECG on their Scanwatch. To control for potential confounders influencing the signal, we asked if they had consumed nicotine, caffeine or alcohol or had a heavy meal in the last 30 min.

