#### Predictive analyses

We will implement both basic and advanced models and compare subsets of data and different timeframes to balance interpretability and predictive performance. With a sample size of at least 350 participants, we have sufficient data to explore a range of methods.

There are various ways to aggregate and preprocess EMA data to include them as predictors of non-response, ranging from simple aggregates to advanced modelling techniques. We will implement dynamic structural equation models (DSEM), an advanced extension of multilevel modelling that integrates time-series dynamics with latent variable modelling.^30^ Multilevel models are considered the gold standard for longitudinal data analysis in psychology,^31^ and DSEM builds on this foundation to allow unequally spaced observations and modelling of time-lagged dependencies, making it well suited for EMA data. The Bayesian estimation approach allows for missing data under the missing at random assumption (eg, when participants skip measurements). Beyond that, DSEM models are extendable to model change in dynamic parameters across measurement bursts. Further, passive data can be flexibly integrated into DSEM to analyse cross-lagged relationships between EMA (ie, affect) and passive sensing features (ie, sleep and physical activity). The model-based framework allows us to derive dynamic parameters (eg, individual autocorrelations and cross-lagged relationships) that we will use as features for the predictive analyses.

For the prediction of NR, basic algorithms include logistic regression, support vector machines, random forests and gradient boosting, depending on the research question and predictors used. Tree-based approaches are known for their effectiveness on tabular data.^32^ Regression-based approaches are highly interpretable. All of the selected require fewer computational resources compared with deep learning models and were frequently applied in psychotherapy research, increasing comparability.^33^,^35^

Advanced modelling approaches will be selected to incorporate the hierarchical, sequential and multimodal structure of our data. These include deep learning architectures like LSTM, Transformers or ensemble learning approaches. To explore how the predictive capacities depend on the time lag, we compare the accuracies of models using subsets of available data (eg, first measurement burst vs second measurement burst) and outcome timepoints (ie, T20 vs TPost).

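### The planned model comparisons cannot show whether EMA predicts non-response through dynamics or through mean level, although the central goal concerns dynamic markers

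*Protocol article*

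**What the plan says.** The Abstract of the Protocol article states the aim: "Our central goal is to determine whether dynamic, multimodal markers derived from EMA and passive sensing can predict treatment non-response". The objectives at the end of the Introduction give the reason EMA should do well: "We expect that EMA-based features can better capture ER-related dynamics and are thus of greatest importance".

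The EMA features are named in two places. Data preprocessing and feature engineering has "For EMA data, we will calculate the RMSSD (that is, for emotional inertia or ER variability), individual SD and mean values". Predictive analyses adds, from the DSEM models, "dynamic parameters (eg, individual autocorrelations and cross-lagged relationships) that we will use as features for the predictive analyses".

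Predictive analyses then fixes the comparisons. A baseline model uses cross-sectional T0 information only (demographics, routine clinical variables, intake questionnaires). Against it stand four sets: "a) EMA-only models, (b) passive-sensor-only models, (c) EMA+passive-sensor models and (d) all data sources combined (T0+EMA + passive". The measure is also fixed: "Paired differences in area under the curve (with 95% CIs, DeLong test) will quantify improvements in discrimination of (non)-response". SHAP values are to describe feature importance. The same section also compares measurement bursts, outcome time points, and basic with advanced algorithms.

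For the affect items, EMA measures says participants "rate on a scale from 1 to 7 how much they currently felt the respective affect".

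**The concern.** The aim is about dynamics, but every listed set is defined by where the data come from. Within the EMA-only set, person means sit beside SD, RMSSD and DSEM parameters, and no listed contrast takes them apart.

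Mean level is a serious rival explanation. Response requires a BSI-GSI below 0.56 plus reliable change, so starting severity plausibly affects who crosses the cut-off. The second response criterion is an aggregate of the same EMA affect items at T20 and TPost, for which the T0 mean is an obvious predictor. A mean over two weeks of beeps measures level more precisely than one intake questionnaire.

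Two things are at stake. A positive EMA result could be read as evidence for dynamic markers when an average produced it. And if the average is enough, the case for eight beeps a day weakens, a burden the Discussion itself acknowledges.

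**Working it through.** **1. The article's own figures.** 585 × 0.80 = 468, as stated for T0. 468 × 0.75 = 351, stated as 350. Beeps per burst: 8 × 14 = 112. Hold-out: 0.20 × 468 = 93.6, about 94 (0.20 × 350 = 70 if only the long version is used). The point does not depend on these, except for precision in step 5.

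**2. Claim against contrasts.**

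| Planned comparison | What differs between the models |
|---|---|
| T0 baseline vs EMA-only | data source; EMA level and dynamics enter together |
| vs passive-only, EMA + passive, all combined | data source |
| first vs second burst; T20 vs TPost | time |
| basic vs advanced algorithms | algorithm, and possibly features |

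No row compares EMA means with EMA means plus dynamics.

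**3. Bound on the SD.** On a 1–7 scale a person with mean m has SD of at most √((m−1)(7−m)). This is 1.66 at m = 1.5, 2.24 at 2, 2.83 at 3, 3.00 at 4, 2.83 at 5, 2.24 at 6 and 1.66 at 6.5. The bound rises to the midpoint and then falls.

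**4. Simulation.** All inputs except the scale and the 112 beeps are assumptions: a latent AR(1) series rounded and clipped to 1–7, no missing beeps, within-person latent SD 1.2, between-person SD 1.0, autocorrelation 0.2, 0.4 or 0.6. Within each scenario SD and autocorrelation are the same for everyone, so nobody differs in dynamics. Non-response depends on the person mean only (log-odds 1 per SD). There were 10,000 patients per scenario, half for fitting and half for the AUC. Ranges run over the three autocorrelations.

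| Average rating | Correlation of mean with SD | AUC, mean only | AUC, SD + RMSSD only |
|---|---|---|---|
| 1.9 | 0.85 to 0.86 | 0.724 to 0.732 | 0.719 to 0.725 |
| 2.6 | 0.73 to 0.77 | 0.725 to 0.750 | 0.687 to 0.701 |
| 4.0 | −0.02 to 0.01 | 0.737 to 0.752 | 0.486 to 0.510 |
| 5.4 | −0.77 to −0.72 | 0.730 to 0.742 | 0.687 to 0.702 |
| 6.1 | −0.86 to −0.85 | 0.726 to 0.752 | 0.719 to 0.745 |

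RMSSD behaves almost like SD. In all scenarios the AUC of mean plus SD and RMSSD, minus the AUC of the mean alone, lies between −0.002 and 0.000. The nested contrast thus correctly shows no dynamic signal where an EMA-only model would look successful. DSEM autocorrelations and cross-lags were not simulated.

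**5. Precision of the nested contrast in the hold-out.** Assume AUC 0.70, 47 non-responders and 47 responders, and a correlation of 0.8 to 0.9 between the two AUC estimates. The Hanley–McNeil terms are 0.70/1.30 = 0.538 and 2 × 0.49/1.70 = 0.576. The variance is [0.21 + 46 × (0.538 − 0.49) + 46 × (0.576 − 0.49)]/47² ≈ 0.0029, so the SE of one AUC is 0.054. The SE of the difference is 0.054 × √(2(1 − r)), which is 0.024 at r = 0.9 and 0.034 at r = 0.8. Multiplying by 2.8 (two-sided 5%, 80% power), the detectable gain is about 0.07 to 0.10.

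**The case against.** The best defence is that dynamics are offered as a rationale and not as a separate hypothesis. The testable content of the objectives is predictive accuracy, the importance of EMA features and the added value of passive ones, and the AUC contrasts are said only to measure discrimination. The plan is also not silent. Comparing data subsets could be read broadly, SHAP reports features one by one, and the all-sources set includes the intake questionnaires, so single-occasion severity is partly accounted for. Procedure and code are placed on OSF and GitHub, which are not shown and may contain a split.

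Part of this stands: the planned AUCs are valid as measures of discrimination, and only their interpretation is at issue. But the Abstract puts dynamic markers in the central goal, and the article lists the sets meant to answer it. SHAP divides credit unstably among features this strongly correlated. The comparison of algorithms can change more than the features. A mean of up to 112 ratings can add level information beyond one questionnaire.

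Three stronger readings are tempting and not supported:

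- **SD and RMSSD rise with the mean throughout.** They do so only below the midpoint of 4. Near 4 there is no linear relation, and above it they fall. The article measures positive as well as negative affect and gives no item means.
- **The scale artefact reaches emotion-regulation variability.** The 1–7 scale is stated for affect only. Response options for the other items are said to be online.
- **EMA performance is not specific to regulation because affect items outnumber regulation items (17 against 8 in Table 1).** The Introduction counts affect among the ER-related constructs, so the item count does not show this.

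**Conclusion.** The point holds as a mismatch between claim and contrast. As written, a gain of EMA over the T0 baseline could come entirely from mean level, and so would not by itself support a conclusion about dynamic markers. This follows from the text and needs no simulation.

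The dependence of affect SD and RMSSD on the mean adds to the problem by an unknown amount. With no true differences in dynamics, the two alone reach an AUC from about 0.5 (average rating at the midpoint) to about 0.7 (average near either end). Which applies depends on item means that the article does not give, and on the assumed simulation inputs. Contamination of the DSEM parameters was not examined.

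Nothing here shows that the planned AUCs are biased, or that dynamics lack predictive value.

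**What to change.** In Predictive analyses, add an EMA-mean-only model as comparator. Report the paired AUC difference with 95% CI between EMA means plus dynamic features (SD, RMSSD, DSEM parameters) and EMA means only, for T20 and TPost. Estimate it in the development-set cross-validation as well as in the hold-out. Optionally, add for the affect items a variability index adjusted for the person's mean, such as the SD relative to the maximum possible at that mean.

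Attribute predictive value to dynamics only to the extent that this contrast supports it. Otherwise limit the conclusion to EMA features predicting non-response.

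The cost is a few extra models and no new data. The drawback is precision: with about 94 hold-out patients, only a gain of roughly 0.07 to 0.10 would be detected reliably under the assumptions above. A null difference should therefore be reported as inconclusive and not as evidence against dynamics. A rule that allows the claim only after a significant hold-out difference would often fail even if dynamics matter.
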